### Statistical methods

2.7

Data with a normal distribution will be expressed as mean ± standard deviation, and categorical data as percentages. Student *t* test, Wilcoxon rank-sum test, Mann–Whitney *U* test, *χ*^2^ test, or Fisher exact test will be applied accordingly. SPSS 23.0 (IBM, Chicago, IL) will be used, and *P* < .05 will be considered statistically significant.

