### Participants studied

2.2

Patients with sustained acute STEMI and suitable for PCI in hospital will be screened. Patients meeting the following criteria will be included:

(1)aging from 18 to 85 years old;(2)diagnosis of acute STEMI within 12 hours;(3)total occlusion of the infarcted artery;(4)blood pressure less than 90/60 mm Hg.

Patients with left bundle-branch block, kidney dysfunction, and histories of myocardial infarction, PCI, coronary artery bypass grafting will be excluded. Before randomization, all patients or authorized persons will sign a written informed consent, and they can freely choose whether to continue the trial at any time.

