### Outcome measures

2.5

The primary outcome is the occurrence of NRP defined as follows: thrombolysis in myocardial infarction flow grade less than 2 without dissection, spasm, or significant residual stenosis, at the end of interventional procedure, and a decrease of less than 50% of the basal elevation of ST segment at 90 minutes after reperfusion with PCI.

The secondary outcomes are levels of interleukin-6 and HS-CRP, cTnT, and CK-MB before, and every 4 hours following PCI, and major adverse cardiovascular events (postinfarction angina, reinfarction, heart failure, arrythmias, cardiogenic shock, and cardiovascular death) at day 30.

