### Sample size

2.6

As previous literature reports, the occurrence of NRP was over 30%.^[5,6]^ We preliminarily found that Nicorandil could reduce the occurrence to 15%, and taking α = 5%, 1-β = 80% with a 2-sided test, 118 cases will be calculated in each group. Considering a potential dropout of 20% in the 30-day-follow-up, 280 cases will be needed in total.

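### All the tests named in Statistical methods are unadjusted; pre-specified adjustment for baseline values already collected would improve precision, clearly for the biomarkers and modestly for no-reflow

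*Protocol article*

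**What the plan says.** Statistical methods (2.7) lists Student's t, Wilcoxon rank-sum, Mann–Whitney U, chi-square and Fisher tests; the list ends "or Fisher exact test will be applied accordingly". All are unadjusted two-sample tests. No regression model or covariate is named.

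Other sections show which values exist before study drug:

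- Outcome measures (2.5) includes "levels of interleukin-6 and HS-CRP, cTnT, and CK-MB before, and every 4 hours following PCI" among the secondary outcomes. Study drug is injected during the procedure (Interventions, 2.4), so the pre-PCI values precede it.
- The ST component of the primary outcome is "a decrease of less than 50% of the basal elevation of ST segment at 90 minutes" after reperfusion. NRP cannot be scored without the basal ST elevation.
- Participants studied (2.2) sets an age range, so age is known for every patient.

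Randomization and blinding (2.3) names no stratification factor. Sample size (2.6) is built on an unadjusted comparison of two proportions: "the occurrence of NRP was over 30"% without treatment, then "We preliminarily found that Nicorandil could reduce the occurrence to 15"%, "taking α = 5%, 1-β = 80% with a 2-sided test", giving "118 cases will be calculated in each group".

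**The concern.** If a baseline variable is related to the outcome, a comparison that ignores it leaves explained variation in the error term. The estimate is then less precise than the collected data allow. Neither the randomisation nor the stated analysis makes any use of baseline risk.

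The issue is plainest for the biomarkers. The plan makes the pre-PCI value part of each biomarker outcome, but the listed tests have no place for it as a covariate. For NRP the same reasoning applies with less force. The outcome is binary, and the gain depends on how well the baseline variables predict it.

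Timing matters as well. A covariate list is credible only if it is fixed before unblinding. If adjustment is added later, it invites the charge that the model was chosen for its result.

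**Working it through.** **1. Reproduce the plan's figure.** Inputs from Sample size: p₁ = 0.30 (the text says over 30%; 30% is used), p₂ = 0.15, two-sided α = 0.05, power 0.80. The unpooled normal formula is

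n = (p₁q₁ + p₂q₂)(z₀.₉₇₅ + z₀.₈₀)² / (p₁ − p₂)²

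= (0.21 + 0.1275) × (1.960 + 0.842)² / 0.15² = 0.3375 × 7.849 / 0.0225 = 117.7, so 118 per group. This matches the plan. The pooled formula gives 121 and the arcsine formula 119.

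**2. Unadjusted power (pooled formula).** 79.2% at 118 per arm; 85.6% at 140 per arm (280 / 2).

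**3. NRP, by formula.** If baseline covariates explain a fraction R² of the outcome variance, the effective sample size is n/(1 − R²) and the confidence interval narrows by the factor √(1 − R²). The protocol gives no R², so a range is assumed.

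| Assumed R² | Power, 118 per arm | Power, 140 per arm | CI narrower by |
|---|---|---|---|
| 0 | 79.2% | 85.6% | 0% |
| 0.02 | 80.0% | 86.3% | 1% |
| 0.05 | 81.2% | 87.3% | 2.5% |
| 0.10 | 83.3% | 89.0% | 5% |
| 0.20 | 87.4% | 92.3% | 11% |

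**4. NRP, by simulation.** 4,000 trials per scenario, 30% against 15%, with one standard-normal baseline covariate. The unadjusted two-proportion test is compared with a logistic model standardised to a risk difference. The odds ratio (OR) per SD is assumed.

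| OR per SD | 118 per arm: unadjusted → adjusted | 140 per arm: unadjusted → adjusted | Variance reduction (118 per arm) |
|---|---|---|---|
| 1.0 | 80.2% → 80.1% | 85.9% → 86.3% | −0.8% |
| 1.25 | 80.4% → 80.7% | 86.0% → 86.5% | 0% |
| 1.5 | 79.5% → 80.8% | 85.6% → 86.8% | 1.9% |
| 2.0 | 80.5% → 83.4% | 85.8% → 88.0% | 6.5% |
| 2.5 | 80.1% → 84.7% | 85.8% → 89.6% | 11.1% |

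The simulation standard error of each power is about √(0.8 × 0.2 / 4,000) = 0.6 points, so differences below about 1 point should not be read closely. At 118 per arm the gain runs from −0.1 to 4.6 points; at 140 per arm it runs from 0.4 to 3.8. With both arms at 22.5% and OR 2.0, type I error is 5.0% adjusted and 4.8% unadjusted.

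A separate simulation of 6,000 trials per scenario used a baseline score with C-statistic 0.64, 0.69 or 0.74. It gave about 81%, 83% and 85% at 118 per arm against about 80% unadjusted, with variance reductions of about 2%, 7% and 12%. The two agree. The R² = 0.20 row in step 3 lies beyond the strongest covariate simulated, so about 5 points is the upper end used here.

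**5. Biomarkers.** Let r be the correlation between the pre-PCI and a post-PCI value, with equal variances σ². Per-patient variances are σ² for the follow-up value alone, 2σ²(1 − r) for the change from baseline, and σ²(1 − r²) with the baseline as covariate. The protocol gives no r.

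| Assumed r | Follow-up only | Change score | Baseline as covariate | Reduction against follow-up only |
|---|---|---|---|---|
| 0.3 | 1.00 | 1.40 | 0.91 | 9% |
| 0.5 | 1.00 | 1.00 | 0.75 | 25% |
| 0.7 | 1.00 | 0.60 | 0.51 | 49% |

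In units of σ², the covariate analysis has the smallest variance in every row.

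**The case against.** The strongest reply is that nothing here is wrong. Chi-square and Fisher tests are valid for a randomised binary outcome. They match the calculation behind 118 per group, and no stratification factor obliges the analysis to adjust. The section is three sentences in a condensed article, and an analysis plan that is not shown may contain an adjusted model. The first part stands in full. The second stands in part: an adjusted model may exist, but the published text does commit to particular tests, and all are unadjusted.

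Three stronger readings are tempting and are not supported.

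- *The trial has no spare power.* A reader might take 20% off 280, reach 224 or 112 per arm, and conclude that the primary comparison falls short of 118. But Sample size ties the dropout to 30-day follow-up, while NRP is settled by 90 minutes after reperfusion. Later dropout need not remove anyone from the primary comparison. With all 140 per arm analysed, unadjusted power is about 86%.
- *The baseline variables are known predictors of NRP.* The Discussion says only that inflammation is among the factors thought to be linked to it, and gives no strength. That lends some support to IL-6 and hs-CRP. For age, basal ST elevation and cTnT the link is assumed; serving as the reference for the ST component does not make basal ST elevation prognostic. The eligibility rule "diagnosis of acute STEMI within 12 hours" does not establish time from onset as a recorded predictor either.
- *Chance imbalance biases the unadjusted result.* It does not. The test's error rate already allows for it, as the simulated 4.8% shows. Imbalance costs precision only.

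**Conclusion.** The point holds as an efficiency improvement. The stated analysis is valid but leaves usable baseline information aside.

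The biomarker part is the better supported: each outcome has its own baseline by design, and the variance falls by 9% to 49% against a follow-up comparison for assumed correlations of 0.3 to 0.7. For NRP the gain is about 0 to 5 power points at 118 per arm, and somewhat less at 140. It is near zero for a weak covariate (OR per SD up to about 1.25), about 1 point at 1.5, 3 points at 2.0 and 4 to 5 points at 2.5. Type I error is preserved, and a useless covariate costs nothing measurable.

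These sizes rest on assumed prognostic strengths and correlations that the protocol does not give, on the plan's 30% and 15%, and on one summary covariate in place of several.

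**What to change.** Amend Statistical methods, or the analysis plan, in two places.

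1. **Biomarkers.** Compare each post-PCI biomarker between groups with its own pre-PCI value as a covariate, by ANCOVA at a given time or a mixed model over the repeated times, on the log scale if the values are skewed.
2. **NRP.** Pre-specify, before unblinding, a logistic model with treatment and a short fixed list of baseline variables already collected, for example age, basal ST elevation and one pre-PCI biomarker such as cTnT or hs-CRP. Report the standardised risk difference with a 95% CI. Keep the unadjusted chi-square test as a sensitivity analysis.

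The cost is a few sentences, slightly more analysis work, and agreeing the covariate list in advance. It needs no new measurements and no extra patients. The sample size can stay as calculated, because the calculation should not rely on an unknown gain from adjustment.

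### Section 2.7 names only two-sample tests for four serially sampled secondary biomarkers; one baseline-adjusted comparison per marker would fit the outcome better

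*Protocol article*

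**What the plan says.** Section 2.5 (Outcome measures) lists among the secondary outcomes "levels of interleukin-6 and HS-CRP, cTnT, and CK-MB before, and every 4 hours following PCI". So each patient contributes a baseline and a series of later values for each of four markers.

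Section 2.7 (Statistical methods) names the Student t test, then "Wilcoxon rank-sum test, Mann–Whitney" U, then the chi-square test, and closes with "Fisher exact test will be applied accordingly". The threshold is P "< .05 will be considered statistically significant". No test is tied to a particular outcome. The rank-sum test and the Mann–Whitney U test are the same procedure, so the list holds two distinct methods for continuous data.

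**The concern.** The outcome is longitudinal with a baseline. The named methods compare two independent groups on one value per patient. That mismatch has two consequences.

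- **Many tests.** Without a model or a summary across time, the direct way to apply these methods is to compare the arms at each sample for each marker, every time at .05. The samples are correlated, but the tests are numerous, and a single significant hour could be reported as evidence of an effect on inflammation or myocardial injury.
- **Unused information.** The pre-PCI value is collected but does not enter a plain two-sample test of later levels. Between-patient variation that the baseline could explain stays in the error term, and a chance imbalance at baseline carries through in proportion to its correlation with the later value.

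**Working it through.** **Inputs from the protocol article.** Four markers; one pre-PCI sample, then one sample per 4 hours (section 2.5); two-sample tests at P < .05 (section 2.7); 118 per group before dropout (section 2.6).

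**Assumptions.** The number of post-PCI samples T is taken as 3, 6, 12 or 18 (12, 24, 48 or 72 hours). Correlation between samples of one marker is 0.7 or 0.9, and between different markers 0.3. The correlation r between the pre-PCI value and the analysed post-PCI value is 0.3, 0.5 or 0.7. The document gives none of these.

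**1. The plan's own group size.** The biomarkers have no power calculation, but 118 is used in step 4. For 30% versus 15%, two-sided 5%, 80% power, unpooled variance:

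(1.960 + 0.842)² × (0.30×0.70 + 0.15×0.85) / 0.15² = 7.849 × 0.3375 / 0.0225 = 117.7, rounded up to 118. It reproduces.

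**2. Chance of at least one P < .05 with no drug effect, if each marker is tested at each post-PCI sample.** The number of tests is m = 4T and the expected number of false positives is 0.05m. Under independence the chance is 1 − 0.95^m; for m = 24, 1 − 0.95^24 = 0.708. For correlated tests, 40,000 multivariate-normal draws were simulated with equal correlation within a marker and 0.3 between markers, counting draws with any |z| > 1.96.

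| T | Tests m | Expected false positives | Independent | Within-marker 0.7 | Within-marker 0.9 |
|---|---|---|---|---|---|
| 3 | 12 | 0.6 | 46% | 34% | 28% |
| 6 | 24 | 1.2 | 71% | 47% | 34% |
| 12 | 48 | 2.4 | 92% | 60% | 41% |
| 18 | 72 | 3.6 | 98% | 68% | 45% |

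The lowest entry, 28%, is still more than five times the nominal 5%.

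**3. One comparison per marker.** Four tests at .05 give 1 − 0.95^4 = 18.5% if independent. A Bonferroni level of 0.05/4 = 0.0125 holds the chance at or below 5%; Holm gives the same protection and is never less powerful.

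**4. Gain from the baseline.** Adjustment multiplies the variance of the arm comparison by 1 − r², so the reduction is r². With 118 per group, the difference detectable with 80% power without adjustment is √(2/118) × 2.802 = 0.365 SD. For that same difference:

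| r | Variance left, 1 − r² | Reduction, r² | Power, baseline-adjusted | Power, change score (variance factor 2 − 2r) |
|---|---|---|---|---|
| 0.3 | 0.91 | 9% | 83.6% | 65.8% |
| 0.5 | 0.75 | 25% | 89.9% | 80.0% |
| 0.7 | 0.51 | 49% | 97.5% | 95.1% |

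**The case against.** The strongest reply is that section 2.7 never says each time point will be tested. A t test or rank test can be applied to a peak, an area under the curve or a change from baseline, and the last of these does use the pre-PCI value. This stands: testing at every sample is an inference from pairing serial levels with two-sample tests, not a statement in the article. A change score would not remove the efficiency point, though. Its variance factor is 2 − 2r, so at r = 0.3 it has less power (65.8%) than ignoring the baseline (80%), and it falls below adjustment at all three correlations in step 4.

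A second reply is that a condensed article may leave the length of sampling, multiplicity for secondary outcomes and model details to a fuller plan. This also stands, and those gaps are not counted here. What remains is that the article does print a list of methods, and that list fits its own outcome poorly.

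A third reply concerns size. Independence is implausible for serial samples from one patient, so 71% is an upper reference, not a forecast. The gain from the baseline rests on an unknown correlation. Section 2.2 admits patients up to 12 hours after diagnosis or onset, so pre-PCI cTnT and CK-MB may be caught at very different stages of release, and the gain for those two may be modest.

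A reader might go further and infer that some time point will probably reach significance by chance. The figures do not support that at six samples: with plausible correlation the chance is 34% to 47%, below one half. A reader might also infer that unadjusted comparisons are biased. They are not: in a randomised trial they are valid on average over chance imbalance, only less precise.

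**Conclusion.** The named methods do not suit the serial biomarker outcomes, and a better method is available using data already planned. If the arms are compared at each sample, the chance of at least one false positive across the four markers is 34% to 47% for six samples at within-marker correlations of 0.9 to 0.7. Over all the correlated cases examined it runs from 28% to 68%. Ignoring the baseline costs precision: adjustment would cut variance by 9% to 49% over r from 0.3 to 0.7, with the low end the more cautious expectation for cTnT and CK-MB. The sample count and every correlation are assumptions, and so is the sample-by-sample testing pattern.

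The consequence is confined to secondary outcomes. The primary NRP comparison and its sample size are untouched. The doubled name for the rank test is editorial.

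**What to change.** In section 2.7, make the secondary analysis of each marker one baseline-adjusted comparison:

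- a linear mixed model on log values over one sampling window, fixed before the data are seen;
- terms for arm, time, arm-by-time and log pre-PCI value, with patient as the repeated unit;
- one contrast, the arm difference averaged over the window, reported with its confidence interval;
- Holm adjustment across the four markers, or an explicit exploratory label for all four;
- individual time points shown descriptively, without tests.

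State the window in section 2.5 and drop one of the two names for the rank test.

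The cost is a change of wording, a stated window and slightly more analysis work; SPSS 23, already named in the plan, can fit such a model. There will be fewer nominally significant time points to report. No new patients or measurements are needed.

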## Discussion

3

Currently, PCI is considered as one of the most effective measures for the treatment of acute STEMI.^[4,14,15]^ Within 12 hours of the onset of STEMI, PCI could rapidly re-canalize the infarcted related arteries, restore myocardial perfusion, and significantly reduce infarct size and mortality in acute STEMI patients. However, coronary angiography studies showed that a large number of patients suffer from NRP, the inadequate reperfusion of the myocardium without evidence of coronary artery obstruction after PCI.^[5,6]^ The phenomenon was thought to be associated with endothelial damage, inflammation, vascular spasm, platelet activation and aggregation, and thromboembolism.^[16,17]^ The NRP can be a marker of myocardial injury, ischemia, infarction, and a predictor of higher incidence of major adverse cardiovascular events. It could seriously affect the prognosis of STEMI patients and increase mortality, which makes it in great significance to prevent and reduce the occurrence of NRP in STEMI patients during PCI.

It has been reported that Nicorandil could improve endothelia, inflammation, fibrinolytic ability, and stabilize plaques,^[18–20]^ and the prophylactic application of Nicorandil before PCI may have the potential to reduce the occurrence of NRP to improve prognosis for acute STEMI. Therefore, to provide higher clinical evidence, we try to conduct a double blinded, randomized, placebo-controlled trial to determine the efficacy of prophylactically intracoronary administration of Nicorandil to reduce the occurrence of NRP during PCI in acute STEMI patients.

Indeed, several limitations need to be addressed. First, there might be bias due to the single-centered study. Second, quantitative analyses for accurately evaluating cardiac function are also needed, such as SPECT and cardiac magnetic resonance.
